### Study design

This is a multicenter pragmatic randomized controlled evaluator-blinded clinical trial of the effectiveness of IMR for CP. We will recruit participants by advertising on the Internet and through posters in hospitals and communities. The recruiting period will be from January 1, 2021, to December 31, 2022.

After explaining the “Guide for Study Subjects” to the participants’ guardian, their consent for clinical study participation will be obtained by the study investigators. The Guide for Study Subjects contains information on the effects of the study and adverse reactions as well as the safety data. The evaluations will be carried out after receipt of the consent forms. On the consent form, participants will be asked if they agree to the use of their data should they choose to withdraw from the trial. Participants will also be asked for permission for the research team to share relevant data with people from the Universities and hospitals taking part in the research. This trial does not involve collecting biological specimens for storage.

The participants will be randomly stratified into groups A and B. Randomization will be performed based on the Gross Motor Function Classification System (GMFCS) stage (stages 1–3 vs. stages 4–5), age (1–2 years vs. 4–6 years), and CP type (spastic vs. non-spastic). The principal researcher will use a block randomization method using a random block size to generate the random allocation sequence. Computer-assisted randomization will be performed using the Excel 2010 program, and the randomized sequences will be delivered in an opaque envelope to conceal allocation. After screening, the researcher will open the sealed envelope in the presence of the participant, and the assignment result will be confirmed.

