**Fig. 1 Fig1:**
[figure not shown]
Flow chart of the study design. First, we will recruit 80 participants from multiple centers. Participants will be randomly assigned to groups A (*n* = 40) and B (*n* = 40) after baseline assessment. Second, all participants will continue UR (physiotherapy, occupational therapy, etc.), as they had been doing previously, throughout the 24-week study period. Third, over weeks 1–12, group A will receive additional IMR comprising acupuncture and herbal medication with UR, and group B is a waiting group that will receive only UR. Participants will be assessed at 12 weeks. Fourth, group B will receive 12 weeks of acupuncture and herbal medication with UR during weeks 13–24; group A will continue UR during weeks 13–24 and return to the institution for follow-up assessment at 24 weeks. The researchers will then collect the results and analyze the data. Abbreviations: UR, usual rehabilitation; IMR, integrative medicine rehabilitation

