**Fig. 2 Fig2:**
[figure not shown]
Standard Protocol Items: Recommendation for Interventional Trials (SPIRIT) schedule of enrollment, interventions, and assessments. GMFCS, Gross Motor Function Classification System; GMFM, Gross Motor Function Measure; K-BSID III, Korean Bayley Scales of Infant Development III; GAS, Goal Attainment Scale; PedsQL, Pediatric Quality of Life Inventory

The assessments will be performed three times in total: at baseline, 12 weeks (after 3 months), and 24 weeks (after 6 months). Two physical therapists with more than 5 years of experience in pediatric rehabilitation will evaluate the scores for each item and the recorded videos (the videos will be recorded by a physical therapist during assessment to evaluate the participants’ GMFM-88, GAS, and K-BSID III developmental status). In principle, the same person should conduct all three evaluations. Assessors will be blinded to the subject assignment, and an inter-rater reliability test will be conducted before each study. The proposed study protocol is schematically presented in Figs. 1 and 2.

Sample size calculations are based on a previous study [8]. We estimated a GMFM-88 score difference of 2.8 ± 3.2 (effect size, *d* = 0.8) which is considered to clinically indicate a change in motor function. A two-sided 5% significance level and 90% power were considered, and calculations indicated the requirement of approximately 28 participants in each group. Estimating a 30% dropout rate, each group will require 40 initial participants. Therefore, this study will be performed as a multicenter randomized controlled trial (RCT) by recruiting 80 subjects for a period of 2 years. Patients will be recruited from Pusan National University Hospital, Yangsan Pusan National University Hospital, Pusan Dongeui Hospital, and Bundang Cha Hospital.

In the event of a direct injury in relation to this study, appropriate medical action may be taken according to the decision of the clinical researcher. The level of compensation shall be an appropriate amount for the nature of the damage, its degree of consistency, and as would be generally decided by the courts in Korea and cover the entire treatment cost until the adverse event (AE) is cured. If rehabilitation therapy is required or an after-effect is noted, appropriate compensation will be provided after assessing the disorder.

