### Statistical analysis

Researchers will analyze for our main objective by comparing the outcomes (GMFM-88) of children receiving UR with IMR (group A) and those receiving UR without acupuncture and herbal medicine (group B) between baseline and 12 weeks. Within-group comparisons for changes in the duration of IMR and UR will be performed. We will use linear mixed models to test group differences in improvements over time for each outcome measure while adjusting for the serial correlation introduced by repeated measurements on the same participants. Group assignment, GMFCS level, time, and their interactions were included as fixed effects, with age as a fixed-effect covariate; patient and patient-by-time effects were included as random effects. A heterogeneous autoregressive covariance structure will be used for the random effects. Rates of change (slopes) from baseline to 12 weeks and from 12 to 24 weeks will be tested to evaluate treatment effects. Rates of change from baseline to 24 weeks will be compared with overall improvement across outcomes. Missing values will be imputed using the last-observation-carried-forward method.

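### Minor: the mixed model leaves the baseline group difference free, so the week-12 effect is a difference in change scores and gives up some precision

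*Protocol article*

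**What the plan says.** The Statistical analysis section of the protocol article sets one modelling approach for all outcomes: "We will use linear mixed models to test group differences in improvements over time for each outcome measure". Its fixed part is given explicitly: "Group assignment, GMFCS level, time, and their interactions were included as fixed effects, with age as a fixed-effect covariate". The contrasts of interest are slopes: "Rates of change (slopes) from baseline to 12 weeks and from 12 to 24 weeks will be tested to evaluate treatment effects". Baseline is thus one of the modelled time points. The baseline score is not listed as a covariate, and no constraint on the baseline means is mentioned. The section adds "A heterogeneous autoregressive covariance structure will be used for the random effects" and "Missing values will be imputed using the last-observation-carried-forward method".

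The outcome sections match this. For GMFM-88, K-BSID III and PedsQL, the evaluation variables are changes across baseline, 12 and 24 weeks.

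The Fig. 1 legend says "Participants will be randomly assigned to groups A" and B, and places this after the baseline assessment. The Study design section names the stratification factors as GMFCS stage in two bands, age and CP type. The baseline value of the outcome is not among them.

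**The concern.** A group main effect, with its interaction with GMFCS level, lets the two arms differ freely at baseline. The treatment effect at week 12 is then the group-by-time term, which is the difference between arms in mean change. Because allocation comes after baseline measurement, any baseline difference is due to chance, and the model spends information estimating it. An analysis that uses the known equality at baseline, or adjusts for the baseline score, has a variance that is no larger in large samples and usually smaller.

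What is at stake is precision, in a trial of 80 children. The same model is meant for every outcome, so the loss need not be the same for a motor score that changes little between visits as for a questionnaire completed by guardians.

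**Working it through.** **1. The plan's own figure.** Inputs from the sample-size paragraph in the Study design section: "We estimated a GMFM-88 score difference of 2.8 ± 3.2", two-sided 5%, 90% power, 30% dropout.

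- n per group = 2 × [3.2 × (1.960 + 1.282) / 2.8]² = 27.45, rounded up to 28.
- 28 / (1 − 0.30) = 40.

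Both stated figures reproduce without any baseline adjustment. (The printed effect size of 0.8 differs from 2.8/3.2 = 0.875; that is a separate matter.)

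**2. Does the model reduce to a difference in change?** The stated structure was evaluated by generalised least squares with 40 per arm, three visits, GMFCS in two strata with all interactions, and age. At unit SD, the variance of the baseline-to-week-12 contrast was:

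- rho 0.5: 0.0500, against 0.0500 for a plain difference in mean change;
- rho 0.9: 0.0100, against 0.0100.

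The two agreed at every correlation tried, under compound-symmetric and autoregressive structures. The GMFCS and age terms do not recover the baseline information.

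**3. Gain from using baseline, equal variances.** Per arm, up to the factor 2/n:

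- change score: 2·SD²·(1 − rho);
- adjusted for baseline: SD²·(1 − rho²);
- ratio: (1 + rho)/2, so the saving is (1 − rho)/2.

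**4. GMFM-88.** The article gives no rho. Assume that 3.2 is the SD of change and that variances are equal. Then rho = 1 − 3.2²/(2·SD²), where SD is the between-child SD (assumed; strictly, the spread left within GMFCS level).

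| Assumed SD | rho | Variance saving | Evaluable n per arm (27.45 × ratio) |
|---|---|---|---|
| 5 | 0.795 | 10.2% | 25 |
| 10 | 0.949 | 2.6% | 27 |
| 20 | 0.987 | 0.6% | 28 |

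Power at 28 per arm is 90.6% unadjusted. It becomes 93.2% at rho 0.8, 91.2% at rho 0.95 and 90.7% at rho 0.99.

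**5. PedsQL and K-BSID III.** No correlation is given; rho 0.5 to 0.7 is assumed.

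- rho 0.5: saving (1 − 0.5)/2 = 25%.
- rho 0.7: saving (1 − 0.7)/2 = 15%.

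LOCF raises the correlation in the analysed data. As an upper bound, suppose that all of the planned 30% drop out before week 12, have baseline carried forward and are otherwise like the rest. Then rho becomes 0.3 + 0.7·rho:

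- 0.5 becomes 0.65, saving 17.5%;
- 0.7 becomes 0.79, saving 10.5%.

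**6. Unequal variances.** With SD 1 at baseline and 1.1 at week 12, the ratio is 1.21(1 − rho²) / (1 + 1.21 − 2.2·rho).

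- rho 0.3: 1.1011/1.55 = 0.71.
- rho 0.9: 0.2299/0.23 = 1.00 (the slope on baseline is 0.9 × 1.1 = 0.99).
- rho 0.99: 0.0241/0.032 = 0.75.

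The gain disappears where the slope of week 12 on baseline is close to 1.

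**7. Chance imbalance.** With equal variances, a baseline difference D is expected to leave rho·D at week 12 without any treatment effect. The change contrast is then off by (1 − rho)·D in size: about 20% of D at SD 5, 5% at SD 10 and 1.3% at SD 20.

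**The case against.** The strongest reply is that nothing here is an error. A repeated-measures model that tests group by time is a standard, valid analysis. It fits the stated aim of comparing improvement and the change-based outcome variables. A reader might infer that the planned estimate is biased, that the test is too liberal or that the trial is too small. The article supports none of these: under randomisation the change contrast is unbiased and keeps its level, and 28 and 40 per group follow from the stated inputs without adjustment.

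A reader might also infer a sizeable loss on the primary outcome. That too lacks support. An SD of 5 looks narrow for children spanning all GMFCS stages. GMFCS level is in the model, so the relevant spread is smaller than the overall one and 5 cannot be excluded, but nothing in the article points to it. The article also does not say whether 3.2 is the SD of change or of the score; under the second reading, rho cannot be derived at all.

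The secondary gain rests wholly on assumed correlations, shrinks under LOCF and can vanish under the heterogeneous variances that the plan allows. K-BSID III is given only to children under 42 months, so its analysis does not involve all 80.

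Finally, it is tempting to say that a change score carries chance imbalance into the result. Only the fraction 1 − rho does so, and stratification limits imbalance in the main prognostic factors.

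All of this stands as a limit on size. It does not remove the point: the method is stated, it does not use a fact the design guarantees, and the alternative needs no new data.

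**Conclusion.** The point holds as a minor improvement that is almost free. The model as written gives a difference in change and forgoes the precision that the measured baseline offers.

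For GMFM-88 the saving in variance is probably small: 2.6% at an assumed SD of 10 and 0.6% at 20, reaching about 10% only at an SD of 5. All three figures assume that 3.2 is the SD of change and that variances are equal. For PedsQL and K-BSID III it is 15% to 25% at an assumed rho of 0.5 to 0.7, or about 10% to 18% in the extreme LOCF case. Near zero is possible if variances change so that the slope on baseline is close to 1. Validity, type I error and the planned sample size are not in question.

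**What to change.** For GMFM-88, K-BSID III and PedsQL, add one sentence to the Statistical analysis section that adopts one of these:

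- Constrain the arms to a common baseline mean: omit the group and group-by-GMFCS terms at baseline and keep their interactions with time.
- Analyse week 12 by ANCOVA on the baseline score, with the planned GMFCS and age terms.

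The baseline scores are already in the Table 2 schedule. The constrained model adds no parameter, and ANCOVA uses one degree of freedom. The sample size need not change. The article was published in August 2020 and dates the start of recruitment to January 2021, so on its own timetable the choice could be fixed before any outcome data exist.

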### Data collection and management

During the recruitment period, researchers will record the baseline characteristics of participants in clinical record forms (CRFs). Data recorded on the original CRFs will be entered into Excel spreadsheets by two data managers independently. The data managers will cross-check the two data sets to ensure accuracy.

All documents related to clinical studies, such as CRFs, should be recorded and distinguished by the subject identification code, usually the subject’s initials, not the name. Records identifying the subject’s identity will be kept confidential, and the identity will also remain confidential on publication of the results of the clinical study.

If a subject prefers to discontinue participation, the researcher can stop the clinical study for the patient and arrange all the planned assessments at the final visit. In the case of a failed follow-up, researchers must demonstrate “reasonable effort” to contact the subject by documenting the actions taken (e.g., telephone contact date, registered mail, etc.) For patients opting to drop-out from the clinical trials, visits should be scheduled as soon as possible to conduct all the planned assessments at the final visit.

The datasets analyzed during the current study will be available from the corresponding author on reasonable request.

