### Monitoring

If one of the following is encountered, it is possible to terminate the clinical trial early: (1) disease condition of the subject deteriorates and it is difficult to continue the research; (2) unexpected systemic diseases that were not detected before the study are diagnosed; (3) the subject or guardian requests the suspension of the examination; (4) self-treatment which may affect the judgment of the study results during the procedure period or the observation period; (5) the occurrence of serious AEs or the patient requires test termination due to AEs; (6) death of the subject; (7) violation of the plan for herbal medicines and medication; (8) subject cannot be tracked; (9) it is difficult for the research to proceed because of the medical staff’s judgment; and (10) treatment compliance is less than 50% (acupuncture or herbal medicine treatment).

Monitoring of clinical trials and auditing trial conduct will be carried out by the company designated by Pusan National University Hospital TKM Clinical Research Center via a regular once-monthly visit or telephonically. A Data Monitoring Committee was not considered as this was a low-risk intervention.

Monitoring personnel will monitor the progress of the clinical study and consult the researcher in case of a problem. Only the Principal Investigator can access the final dataset, and statisticians will be provided with a dataset blinded to group allocation. However, the TKM doctor cannot be blinded to group allocation, because acupuncture is possible only when the participant and the TKM doctor have contact.

Protocol amendments will be performed based on consensus by the Pusan National University Hospital TKM Clinical Research Center, and researchers will update the protocol in the Ministry of Food and Drug Safety Integrated Information System.

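### Carrying the last observation forward shrinks the 12-week GMFM-88 effect, and the planned mixed model does not need it

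*Protocol article*

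**What the plan says.** The primary comparison in the Statistical analysis section sets group A against "those receiving UR without acupuncture and herbal medicine (group B) between baseline and 12 weeks". The model is stated as "We will use linear mixed models to test group differences in improvements over time for each outcome measure", with slopes from baseline to 12 weeks and from 12 to 24 weeks tested. The same paragraph ends: "Missing values will be imputed using the last-observation-carried-forward method". It names no other method for missing data.

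The Study design section schedules assessments at baseline, 12 and 24 weeks only. Its sample-size paragraph states: "Estimating a 30% dropout rate, each group will require 40 initial participants". It does not split that rate by group or by time.

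Two further sections bear on what is carried forward:

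- **Data collection and management** says of children who opt to drop out that "visits should be scheduled as soon as possible to conduct all the planned assessments at the final visit".
- **Monitoring** lists ten grounds on which early termination is possible. One is "10) treatment compliance is less than 50% (acupuncture or herbal medicine treatment"). Another, ground 7, concerns violating the plan for herbal medicines and medication.

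**The concern.** A linear mixed model fitted by likelihood uses every observed value and is valid under missing-at-random without imputation. Filling the gaps first replaces that assumption with a less plausible one: that a child aged 2–6 who continues rehabilitation stops changing at the last visit. It also treats the filled-in values as observed data.

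For the primary comparison the last value is usually baseline, so the imputed change is exactly zero. Zeros in both groups dilute a real difference. If the groups lose different shares, and children improve in both, the zeros also create a difference where none exists.

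The sample size rests on the opposite idea. The increase from 28 to 40 per group treats dropouts as giving no information, whereas the analysis puts them back as if they had been measured.

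**Working it through.** **Inputs from the protocol article.** Difference δ = 2.8 and SD 3.2 ("We estimated a GMFM-88 score difference of 2.8 ± 3.2"); "A two-sided 5% significance level and 90% power were considered"; 28 evaluable and 40 enrolled per group; 30% dropout.

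**Inputs assumed, because the article gives none.** The 12-week gain g in group B, taken as 1 to 3 points; the share lost before week 12 in each group, dA and dB; and the share f of a child's gain already present at an exit visit.

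**Step 1: the plan's own figures.** n = 2 × (1.96 + 1.2816)² × (3.2/2.8)² = 27.4, so 28 per group; 28/(1 − 0.30) = 40. Both reproduce. (They use 2.8/3.2 = 0.875; the printed d = 0.8 would give 33. That is a separate matter.) Power with 28 completers per group is 90.6%.

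**Step 2: expected difference when baseline is carried forward.** Lost children score 0, so

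E = (1 − dA)(g + δ) − (1 − dB)g = δ(1 − dA) − g(dA − dB).

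With an exit visit, replace dA and dB by dA(1 − f) and dB(1 − f).

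| Loss by week 12, A/B | Exit visit | Expected difference |
|---|---|---|
| 30% / 30% | none | 2.8 × 0.70 = 1.96 |
| 15% / 15% | none | 2.8 × 0.85 = 2.38 |
| 30% / 30% | half the gain captured | 2.8 × 0.85 = 2.38 |

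With equal loss, g drops out of the estimate. It affects only the variance.

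**Step 3: power at 30%/30% with no exit visits.** The variance of change in a group with mean change m is (1 − d) × 3.2² + d(1 − d)m². For g = 2:

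- Group A: 0.7 × 10.24 + 0.21 × 4.8² = 12.01.
- Group B: 0.7 × 10.24 + 0.21 × 2² = 8.01.
- SE = √((12.01 + 8.01)/40) = 0.707.
- Power = Φ(1.96/0.707 − 1.96) = 79%.

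The same formula gives 84% at g = 1 and 73% at g = 3. Simulated t-tests on change gave 84%, 78% and 72% for g = 1, 2 and 3.

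The other cases are milder. At 15% loss the simulated power is about 93% to 87% for g = 1 to 3. The 34 completers per group (40 × 0.85) would give Φ(0.875 × √17 − 1.96) = 95%. With half the gain captured at exit visits, power is not lost, but the estimate is still 15% too small.

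**Step 4: no true effect.** Set δ = 0, so E = −g(dA − dB). With equal loss E = 0 and the type I error stays at 5%. With unequal loss and g = 3 in both groups:

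- A 40%, B 20%: E = −0.6, against IMR.
- A 20%, B 40%: E = +0.6, in favour of IMR.

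For the first case, SE = √((8.30 + 9.63)/40) = 0.670 and 0.6/0.670 = 0.90. Rejection is Φ(0.90 − 1.96) + Φ(−0.90 − 1.96) ≈ 15%, of which only 0.2% is in favour of IMR. In the second case the two tails swap. At g = 2 the shift is 0.4 and rejection about 10%.

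**Step 5: can the rules produce unequal loss?** In weeks 1–12 only group A receives acupuncture and herbal medicine. Ground 10 and the herbal part of ground 7 can therefore remove only group A children before the primary endpoint. The other grounds name no group.

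**The case against.** **Gaps mainly in group A.** A reader might infer that the termination rules create missing data mainly there. The article does not support that. The grounds are discretionary and no rates by group are given. Only ground 10 and the herbal part of ground 7 are exclusive to group A in weeks 1–12. Adverse events may also fall more on A, but self-treatment could fall on the waiting group.

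**A false benefit.** A reader might also infer that the method tends to produce a spurious benefit of IMR. More loss in A works against IMR; only more loss in B works for it; equal loss does neither.

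**The 30% as a week-12 rate.** The article gives no timing, and losses after week 12 leave the primary comparison untouched. The 1.96 is therefore an upper case.

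**Exit visits.** They are planned, so zero change is not automatic. This stands, and it softens the bias. But an early score still stands in for week 12, and the text speaks of those who choose to leave, without expressly covering children removed under Monitoring.

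**Left to the analysis plan.** A sensitivity analysis often is. The LOCF sentence itself is not an omission: the article states the method.

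**Approximation.** The figures come from a comparison of mean change, not from the full mixed model, and the control gains are assumed.

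**Conclusion.** The point holds as an attenuation problem in the primary analysis. Under the plan's own δ, the estimate falls from 2.8 to 1.96 (−30%) if the whole 30% is lost by week 12 in both groups with no exit visits. It falls to about 2.38 (−15%) under 15% loss, or if exit visits capture half the gain. In the upper case power drops from about 90% to between 84% and 72% for assumed control gains of 1 to 3 points. The 30% shrinkage does not depend on the assumed gain; the power does.

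Bias from unequal loss is possible, but its size and sign are unknown. The shift of 0.6 points with 15% rejection needs 40% against 20% loss and a 3-point gain in both groups, and shows only what such an imbalance would do.

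**What to change.** In Statistical analysis, delete the LOCF sentence. State that the mixed model is fitted to all observed data in the groups as randomised, and that any assessment brought forward is entered at its actual date. Add one sensitivity analysis for departures from missing-at-random, for example multiple imputation with shifted values, unless the analysis plan already has one.

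In Monitoring, add that meeting a listed ground does not by itself end outcome assessment. The child is still assessed at 12 and 24 weeks if alive, traceable and without withdrawn consent. The treatment-stopping grounds stay as they are.

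The cost is a few sentences, some extra follow-up effort and one more analysis. The sample size does not change. The article dates recruitment from January 2021, after its August 2020 publication, so on those dates the change could precede any data.
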